### Procedure for unblinding if needed {17b}

As the trial is single-blind, patients interested in knowing their group could be informed by the investigator following the analysis of results.

## Data collection and management

### Plans for assessment and collection of outcomes {18a}

This study is an internal multicenter clinical trial. All data collection physicians will be specially trained by assessors. We will conduct regular online meetings to share the progress of the trial and discuss the problems encountered during the project. Moreover, we will conduct field visits to subcenters for quality control. We shall also regularly organize the trial data to check for any missing data, and to promote data quality, we intend to apply other methods and call the participants as well.

### Plans to promote participant retention and complete follow-up {18b}

Not applicable, as the trial will not involve follow-up; thus, we have no plans to promote participant retention and complete the follow-up.

### Data management {19}

The case report form (CRF) of the respective patients will be entered and/or filled in for all the collected patient data during this clinical trial. The study number, subject number, date of subject information, and informed consent will be appropriately documented in the patient CRF. We will archive the source data as per GCP guidelines. The data manager will be responsible for data processing and will conduct regular monitoring according to the sponsor’s standard operating procedures to ensure that the dates are adequate, accurate, and complete. The source data lock will occur only after the completion of the quality assurance procedures.

### Confidentiality {27}

Participant information will be confidential and managed according to the Data Protection Act, NHS Caldecott Principles, The Research Governance Framework for Health and Social Care, and the conditions of Research Ethics Committee approval. The confidentiality of the data collected during the course of the research will be strictly maintained, and only the members of the trial team (or individuals from the sponsor organization or center sites relevant to the trial) will be allowed to access the data. All documents containing patient information are stored in a specific cabinet in the anesthesia department, locked and keyed for safekeeping. The permission of the principal investigator is required for the removal or access of the data. The participants will be allocated an individual trial identification number and their details will be stored in a secure database. This database is maintained by professional researchers, and only the principal investigator has access to the data set. The anonymized trial data are not to be shared with other researchers.

### Plans for collection, laboratory evaluation, and storage of biological specimens for genetic or molecular analysis in this trial/future use {33}

Not applicable as no biological specimens were collected as part of this trial.

## Statistical methods

### Statistical methods for primary and secondary outcomes {20a}

#### Data selection for statistical analysis

Full analysis set (FAS): According to the principle of intention-to-treat analysis, the full analysis set will include all subjects who are randomized to the study and receive the study treatment.Per-protocol set (PPS): The PPS population will include all FAS patients without major protocol deviations that influence the evaluation of primary outcomes, such as the different dosages of sufentanil during the induction or lack of primary outcome data. The efficacy analysis will be performed on the FAS and PPS.Safety analysis set (SAS): The safety population will comprise all subjects who receive the study treatment. Analyses of safety data in the study will be based on the safety population.

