### Methods in the analysis to handle protocol nonadherence and any statistical methods to handle missing data {20c}

Statistical analysis was performed based on intention-to-treat. Regardless of protocol adherence, the results of the outcome analyses will be randomly analyzed. The frequency and type of missingness of all the variables will be screened. If missingness is >5% of any variable, we will use multiple imputations. Complete case analysis will be performed as a sensitivity analysis, in case of missing data and imputation.

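### The full analysis set is labelled intention-to-treat but admits only patients who received the study treatment, which conflicts with the protocol's own adherence statement and can exclude patients unevenly by arm

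*Protocol article*

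**What the plan says.** Three statements bear on who is analysed.

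- **Full analysis set (FAS)**, Data selection for statistical analysis. After invoking the intention-to-treat principle, the protocol article says "the full analysis set will include all subjects who are randomized to the study and receive the study treatment".
- **Safety set**, same section: "The safety population will comprise all subjects who receive the study treatment". The condition on treatment is the same as for the FAS.
- **Section {20c}**, on nonadherence and missing data: "Statistical analysis was performed based on intention-to-treat". The next sentence reads "Regardless of protocol adherence, the results of the outcome analyses will be randomly analyzed".

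On which set carries efficacy, the first section says only "The efficacy analysis will be performed on the FAS and PPS". The per-protocol set (PPS) removes FAS patients with major deviations, "such as the different dosages of sufentanil during the induction or lack of primary outcome data".

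The context comes from elsewhere in the article. Section {6b} makes standard monitoring alone the comparator, and {11a} gives standard monitoring to both groups. Section {17a} blinds participants only. Table 3 places randomisation at arrival in the examination room, before sedative induction.

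**The concern.** An intention-to-treat set keeps every randomised patient in the assigned arm. A set that also requires receipt of treatment is conditioned on something that happens after randomisation. In a blinded drug trial that condition often does little harm, because failure to receive treatment has no link to the arm. Three features make it less safe here.

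1. The treatment is a way of monitoring. A control patient receives it as soon as routine monitoring is attached. A capnography patient receives it only if the sampling line and display are actually used.
2. The staff who decide whether capnography is used know the allocation.
3. There is an interval between randomisation and induction in which use can fail or be abandoned.

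If patients in whom capnography was not used differ in their risk of hypoxia, removing them from one arm only would shift the comparison on which the superiority claim rests.

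**Working it through.** **Step 1: the statements side by side.** Take a patient assigned to capnography whose line fails and who is managed on pulse oximetry alone.

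| Rule | Is the patient analysed for efficacy? |
|---|---|
| FAS definition, read literally | No: randomised, but study treatment not received |
| Section {20c}, intention-to-treat whatever the adherence | Yes, in the capnography arm |
| Safety set | No, by the same condition as the FAS |

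The first two rows contradict each other. The third shows that the FAS is in substance the treated population under an intention-to-treat label.

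**Step 2: is the key term defined?** The article does not say what receiving the study treatment means for a monitoring intervention. The control set-up is not settled either: {11a} says that no sampling line is connected in the blinded arm, while {16b} and {17a} describe the same cannula connected to the monitor in both groups.

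**Step 3: the form of the possible bias.** Let *p* be the true hypoxia risk in the capnography arm, *f* the fraction of that arm excluded for non-use, and *r* the risk among those excluded. The risk in those who remain is (*p* − *f r*)/(1 − *f*), so the shift is *f*(*r* − *p*)/(1 − *f*). It is zero if *r* = *p*, flatters capnography if *r* > *p*, and goes the other way if *r* < *p*. The document gives neither *f* nor *r*.

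For scale only, take *p* = 8% (the control rate in {14}, i.e. no effect), and assume *r* = 16%, twice *p*:

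- *f* = 1%: 0.01 × 8 / 0.99 = 0.08 percentage points
- *f* = 5%: 0.05 × 8 / 0.95 = 0.42 points
- *f* = 10%: 0.10 × 8 / 0.90 = 0.89 points

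The planned difference is 8% − 4% = 4 points. These values of *f* and *r* are assumptions, not estimates.

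**Step 4: what keeping everyone costs.** The plan's total of about 1800 is not in dispute. The continuity-corrected formula for 8% against 4%, two-sided 5%, 90% power, gives 788 per arm; 2 × 788 / 0.90 = 1751.1, or 1752 with each arm rounded up, close to 1800. If a fraction *f* of the capnography arm does not use it and those patients have the control risk of 8%, the expected difference becomes 4 × (1 − *f*) points. Power at 900 per arm (pooled z test) is then:

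| Assumed non-use *f* | Expected difference | Power |
|---|---|---|
| 0% | 4.00 points | 94.7% |
| 1% | 3.96 points | 94.3% |
| 5% | 3.80 points | 92.1% |
| 10% | 3.60 points | 88.7% |

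These powers assume that every outcome is observed.

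**The case against.** The best defence is that one-sided exclusion is conjecture. A failed line is plainly nonadherence, which {20c} says does not affect analysis. Consent, randomisation and procedure fall in one visit, so few patients should be randomised and not treated. If the phrase means only patients who never had a sedated procedure, exclusion has no built-in asymmetry. Much of this stands: the article does not show that such exclusions will occur, or how many. It does not remove the contradiction, because the benign reading has to be supplied by the reader and the literal one is available.

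A reader might infer more than the document supports.

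- **That no set leads.** The first section does not rank FAS and PPS. But {20c} makes intention-to-treat the basis of analysis, and that principle is tied only to the FAS, so the FAS is the implied lead. This deserves a sentence; it is not a free choice between two sets.
- **That the sufentanil criterion compromises the efficacy claim.** It affects only the PPS, a set built by removing deviations.
- **That the missing-data rule leaves the result exposed.** The rule is "If missingness is >5% of any variable, we will use multiple imputations". With 5% missing (0.05 × 900 = 45 per arm), complete cases at the design rates are about 68 and 34 events of 855. Giving 4 events to the 45 missing controls makes 72/900. Significance is lost once 18 of the 45 missing capnography patients are hypoxic: 72/900 against 52/900, p = 0.063. That is 18/45 = 40%, against an assumed 4% in that arm, for an outcome measured in one visit under continuous monitoring. A tipping-point analysis would be a preference, not the correction of an error.

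**Conclusion.** The concern holds as an inconsistency in the definition of the main analysis set. The FAS carries an intention-to-treat label, uses the treated-only condition of the safety set, and conflicts with {20c}. Because the intervention is monitoring applied by staff who know the arm, and the comparator is given to everyone, the literal rule can act mainly on the capnography arm.

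It would go too far to say that randomisation has been broken. That would need evidence that patients will be excluded for non-use and that their risk differs, and the article has neither. The size cannot be computed from the document and may be small. The conclusion rests on the plain wording and on the asymmetry between the arms, not on the illustrative shifts above. It should be corrected because the set decides who counts in the primary comparison and the correction is cheap.

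**What to change.** 1. Define the FAS as all randomised patients, analysed in the assigned arm whatever monitoring was actually used.
2. If any exclusion is kept, limit it to patients whose sedated procedure never started, and report their number and reasons by arm.
3. State that the superiority claim rests on this set and that the PPS analysis is supportive.
4. In {20c}, correct the end of the sentence on adherence so that it says outcomes are analysed as randomised.

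The cost is wording only. The planned sample size does not change. The estimate may be slightly diluted by patients in whom capnography was not used, in proportion to 1 − *f* if those patients carry the control risk.

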#### Statistical analysis plan

All statistical analyses in this trial will be programmed and calculated using Statistical Package for the Social Sciences version 23.0 (IBM Inc., Armonk, NY, USA). The normally distributed baseline continuous data will be represented by mean (standard deviation [SD]) and compared by using an unpaired *t*-test. The non-normally distributed continuous data will be presented as median (interquartile range [IQR]) and compared by using Mann–Whitney *U* test. We will use χ^2^ test, continuity correction *χ*^2^ test, or Fisher’s exact test to analyze the categorical variables. We intend to compare the incidences of hypoxia, subclinical hypoxia, severe hypoxia, and total hypoxia of the participants during gastrointestinal endoscopy under sedation via *χ*^2^ test, continuity correction *χ*^2^ test, or Fisher’s exact test.

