### Sample size {14}

Our previous study revealed that hypoxia incidence in patients during gastrointestinal endoscopy with propofol sedation was ~8 % [11]. The anticipated effect size of additional capnographic monitoring was 50%, implying that the hypoxia incidence power analysis assumes a reduction from 8% to 4%. The results of a conventional analysis were compared between the capnography-open and capnography-blinded groups to detect differences in proportions (hypoxia). We use PASS 11.0, randomization 1:1, power of 1 − β = 0.90, and a two-sided α level of 5%. We assume a 10% dropout rate. Thus, the results revealed that ~1800 patients would be required.

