## Assignment of interventions: allocation

### Sequence generation {16a}

In this trial, we used stratified blocked randomization to design the central randomization system. Risk factors for hypoxia during sedated gastrointestinal endoscopy include patient factors, sedation factors, and endoscopic operation factors. Patient factors mainly include preexisting cardiopulmonary disease, obesity, and advanced age. The incidence of hypoxia during sedated gastrointestinal endoscopy varies among patients with different underlying conditions. However, the subjects in our trial were all ASA I–II patients and did not include patients with ASA III-IV, which means that the trial did not involve patients with previous severe cardiopulmonary disease. Additionally, the number of obese patients in the older population in China is extremely low, and stratification by obesity would provide little benefit. Our study only included ASA I–II older patients aged 65 to 80 years, who we can assume have similar physical conditions, and the incidence of hypoxia during sedated gastrointestinal endoscopy is approximately the same. Therefore, we did not stratify them by age, and only central stratification was used in our trial. Complete baseline data will be collected from participants, including name, gender, date of birth, etc. After assessing patient eligibility for inclusion, his/her informed consent will be obtained. We will randomly assign the participants in a ratio of 1:1 to the standard or additional capnographic monitoring group according to the allocation sequence of the central randomization system. The length of a random sequence is not fixed, and 4, 6, and 8 are random.

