### Methods for additional analyses (e.g., subgroup analyses) {20b}

The association between the baseline characteristics and intervention and the risk of total hypoxia cumulative incidence was examined using univariable- and multivariable-adjusted logistic regression models. The results were presented as the odds ratios and corresponding 95% confidence intervals.

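### Randomisation is stratified by centre, but the primary test of hypoxia incidence ignores centre: mildly conservative if centres differ, and free to correct

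*Protocol article*

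**What the plan says.** Under Sequence generation {16a}, the protocol article describes stratified blocked randomisation. It considers age and obesity as strata, rejects both, and concludes: "Therefore, we did not stratify them by age, and only central stratification was used in our trial". Eligibility criteria {10} states that three centres recruit, so in context this means stratification by centre.

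The primary outcome, under Outcomes {12}, is the incidence of hypoxia. Its analysis is given under Statistical analysis plan: "We intend to compare the incidences of hypoxia, subclinical hypoxia, severe hypoxia, and total hypoxia of the participants during gastrointestinal endoscopy under sedation via" a chi-square test, a continuity-corrected chi-square test or Fisher's exact test. All three compare two pooled groups, and centre appears in none of them.

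Methods for additional analyses {20b} adds a regression: "the risk of total hypoxia cumulative incidence was examined using univariable- and multivariable-adjusted logistic regression models". Its outcome is total hypoxia rather than the primary outcome, and centre is not named among its covariates.

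**The concern.** Blocking within centre forces the arms to be nearly balanced at each hospital. Differences between hospitals in the underlying hypoxia rate then contribute almost nothing to the chance difference between arms. A pooled chi-square test still counts that between-centre variation in its variance. Its standard error is therefore too large whenever centres differ, the nominal 5% test rejects less often than 5% under the null, and some power bought by the design is not used.

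What is at stake is efficiency and agreement between design and analysis. The error is in the cautious direction, so a false claim of benefit is not made more likely.

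**Working it through.** **Inputs from Sample size {14}.** Control rate: "hypoxia incidence in patients during gastrointestinal endoscopy with propofol sedation was ~8" percent. Effect: "implying that the hypoxia incidence power analysis assumes a reduction from 8% to 4" percent. Significance: "a two-sided α level of 5" percent. Power and allocation: "We use PASS 11.0, randomization 1:1, power of 1 − β = 0.90". Dropout: "We assume a 10% dropout rate". Three centres, from Eligibility criteria {10}.

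**Step 1: reproduce the plan's figure.** Without continuity correction, n per arm = [1.96·√(2·0.06·0.94) + 1.2816·√(0.08·0.92 + 0.04·0.96)]² / 0.04² = 739. With the continuity correction it is 788 per arm. Dividing by 0.9 and rounding up gives 876 per arm, 1752 in total, which is within 3% of the stated ~1800. The uncorrected formula gives 1644 in total. The stated size is therefore reproduced, most closely with the correction.

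**Step 2: evaluable patients.** 1800 × 0.9 / 2 = 810 per arm. With equal centres (an assumption) that is 270 per arm per centre.

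**Step 3: size of the pooled test in closed form.** Let p̄ be the mean rate over centres and B the variance of the centre rates about p̄. The pooled test uses the variance p̄(1−p̄). With balance within centres the true value is p̄(1−p̄) − B. The actual size is therefore about 2·Φ(−1.96·√r), with r = p̄(1−p̄) / [p̄(1−p̄) − B]. All the scenarios below have p̄ = 8%, so p̄(1−p̄) = 0.0736. The centre rates are assumed, because the article gives none.

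- 8/8/8%: B = 0, r = 1, size 5.0%.
- 4/8/12%: B = (0.04² + 0 + 0.04²)/3 = 0.00107, r = 0.0736/0.07253 = 1.015, size 4.8%.
- 2/6/16%: B = (0.06² + 0.02² + 0.08²)/3 = 0.00347, r = 0.0736/0.07013 = 1.049, size 4.5%.
- 1/3/20%: B = (0.07² + 0.05² + 0.12²)/3 = 0.00727, r = 0.0736/0.06633 = 1.110, size 3.9%.

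**Step 4: simulation of pooled chi-square against Cochran-Mantel-Haenszel (CMH) by centre.** 270 per arm per centre.

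| Control rates by centre (assumed) | Size, pooled v CMH | Power, risk halved in each centre | Power, planned odds ratio in each centre |
|---|---|---|---|
| 8/8/8% | 4.9% v 4.9% | – | 93.1% v 93.1% |
| 6/8/10% | – | 93.0% v 93.0% | – |
| 4/8/12% | 4.8% v 5.0% | 93.1% v 93.2% | 92.6% v 92.8% |
| 2/6/16% | 4.4% v 5.0% | 93.4% v 93.9% | 91.9% v 92.4% |
| 1/3/20% | 3.9% v 5.0% | 93.7% v 94.6% | – |

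A dash marks a combination not run. The simulated sizes agree with Step 3 to within 0.1 point. The power loss runs from nothing, through 0.1 to 0.2 points at 4/8/12%, to 0.9 points at 1/3/20%.

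**Step 5: which of the three listed tests would apply.** Expected events at the planned rates are 810 × 0.08 + 810 × 0.04 = 64.8 + 32.4 = 97.2, so the smallest expected cell is 97.2/2 = 48.6. By the usual cell-count convention this calls for the ordinary chi-square. Exact power at 810 per arm is 93.0% for the ordinary test and 91.5% for both the corrected test and Fisher's test. All are above 90%.

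**The case against.** The strongest reply is that nothing is broken. The pooled test never exceeds 5%, every scenario keeps power above the planned 90%, and with moderate centre differences the loss is 0.2 points or less. The Discussion describes the sites as hospitals of one grade, and eligibility is the same at each, so an eightfold or twentyfold spread in rates is an extreme assumption. All of this stands, and it limits the weight of the point. It does not remove the mismatch: centre was chosen as the only stratum, and the analysis drops it.

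A reader might infer more, and the documents do not support it:

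- *The choice among three tests leaves the deciding test open.* The list is given once for four endpoints, including the rarer severe hypoxia. At the planned rates the cell counts point to the ordinary chi-square for the primary outcome. A selection rule is detail that an analysis plan commonly supplies.
- *The primary result will have no effect estimate.* The article is silent on this, but effect measures are commonly left to the analysis plan, which is not shown.
- *The adjusted model has been moved to the wrong endpoint.* It is listed as an additional analysis, and it contradicts nothing in the primary one.
- *The corrected or exact tests leave the trial short of power.* The stated sample size is best reproduced with the continuity correction, so that cost appears to have been paid already.
- *Age, obesity and similar factors must enter the primary analysis.* Sequence generation {16a} names them as general risk factors, but then argues that they vary little in this population.

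**Conclusion.** The point holds as a small improvement in efficiency and consistency. Randomisation is stratified by centre, and the stated primary comparison is not. The consequence is mild conservatism if centres differ: size 4.8% to 3.9% instead of 5.0%, and about 0.2 to 0.9 points of power, over assumed control rates of 4/8/12% to 1/3/20%. If the centres share one rate the cost is nil. Type I error is not inflated, and power remains above 90% throughout.

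These figures rest on 810 evaluable patients per arm, equal centre sizes, a mean control rate of 8% and the planned effect. The centre rates are assumptions. It would be wrong to conclude that the planned test is invalid or that the trial is underpowered.

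**What to change.** Under Statistical analysis plan, name a single primary analysis of hypoxia incidence: a Cochran-Mantel-Haenszel test stratified by centre, or logistic regression with arm and centre. State the matching centre-adjusted risk difference or risk ratio with its 95% confidence interval for the primary outcome. For orientation, at the planned rates with 810 per arm and no centre differences, the risk difference would be 4.0 points (0.04 ± 1.96·√[(0.08·0.92 + 0.04·0.96)/810], about 1.7 to 6.3). The risk ratio would be 0.50 (about 0.33 to 0.75). Keep the continuity-corrected or exact tests for sparse secondary events.

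Do not extend the adjustment to body mass index or procedure type, because the article does not name either as collected.

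The cost is wording only. Centre is known for every patient through the randomisation system, and the sample size is unchanged. Logistic regression is already foreseen under Methods for additional analyses {20b}. No interim analysis is planned, so the change can be made before the data are locked, with the ethics committee's consent that the article requires for protocol changes.
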